# The effect of repeated remote ischemic postconditioning on infarct size in patients with an ischemic stroke (REPOST): study protocol for a randomized clinical trial

**DOI:** 10.1186/s13063-019-3264-0

**Published:** 2019-03-15

**Keywords:** Stroke, Ischemia, Ischemic conditioning, Infarct size, Clinical outcome

## Abstract

**Background:**

Remote ischemic postconditioning (rIPostC) refers to the observation that repeated, short periods of ischemia protect remote areas against tissue damage during and after prolonged ischemia. Based on previous observations of a potential neuroprotective effect of rIPostC, the aim of this study is to evaluate whether repeated rIPostC after an ischemic stroke can reduce infarct size, which could be translated to an improvement in clinical outcomes.

**Methods/design:**

We will enroll 200 ischemic stroke patients to daily rIPostC or sham conditioning during hospitalization into a randomized single-blind placebo-controlled trial. The intervention consists of twice daily exposure to four cycles of 5-min cuff inflation around the upper arm to > 20 mmHg above systolic blood pressure (i.e., rIPostC) or 50 mmHg (i.e., control), followed by 5 minutes of deflation. The primary outcome is infarct size, measured using an MRI diffusion-weighted image at the end of hospitalization. Secondary outcomes include the Modified Rankin Scale, National Institutes of Health Stroke Scale, quality of life, and cardiovascular and cerebrovascular morbidity and mortality. To explore possible underlying mechanisms of rIPostC, venous blood will be sampled to assess biomarkers of inflammation and vascular health.

**Discussion:**

Previous studies in animals and humans, using a single bout of remote ischemic conditioning, report a potential effect of rIPostC in attenuating neural damage. Although repeated rIPostC has been investigated for cardiovascular disease patients and preclinical stroke models, no previous study has explored the potential physiological and clinical effects of repeatedly applying rIPostC during the hospitalization phase after a stroke.

**Trial registration:**

Netherlands Trial Register, NTR6880. Registered on 8 December 2017.

**Electronic supplementary material:**

The online version of this article (10.1186/s13063-019-3264-0) contains supplementary material, which is available to authorized users.

## Background

Ischemic stroke is the leading cause of disability in adults worldwide and has the second highest mortality of all cardiovascular diseases [1]. In particular, the intravenous and endovascular treatment of ischemic stroke has markedly improved survival and long-term functional outcomes [2–4]. Unfortunately, a substantial number of stroke patients still end up with a physical disability. This may in part be because the therapeutic window to attenuate the detrimental impact of ischemic injury is limited to 6 hours after the stroke. Currently, there are no subsequent treatment options available [5], although some recent studies have had promising results for intra-arterial therapy in specific subgroups of stroke patients [6, 7]. Moreover, acute revascularization might induce ischemia reperfusion injury [8] and glutamatergic excitotoxicity [9], which could lead to additional damage in the ischemic penumbra. This highlights the need for innovative additional treatment options, which preferably would extend beyond the 6 hours post-stroke. Identification of such treatment options may have a significant impact on the burden of stroke for individual patients, their caregivers, health-care professionals, and at the socioeconomic level.

A potential approach may be the application of remote ischemic postconditioning (rIPostC). Remote ischemic conditioning (RIC) consists of several cycles of brief periods (5 min) of limb ischemia followed by reperfusion, which can be applied by inflating a simple blood pressure cuff. This intervention subsequently confers protection against severe ischemia in remote organs in humans [10–12]. Due to the unpredictability of stroke, applying RIC before the event is not possible. However, similar protective effects are present when RIC is applied during or even after an ischemic insult [13], which is known as rIPostC. Whilst the majority of studies have focused on the protective effects of ischemic pre- and postconditioning on cardiac tissue [10–12, 14, 15], recently, several studies have supported the ability of rIPostC to reduce neural damage after reperfusion [8, 16–19], validating that rIPostC may have clinical potential for stroke patients, with clinical trials showing promising results [20, 21]. Additionally, Hess et al. postulated that, in addition to the short-lasting benefits of a single bout of conditioning, chronic benefits may be induced with repeated daily conditioning [18]. This has since been supported by preclinical studies in mice and rats [22, 23] and further supported by evidence from clinical trials in humans with favorable clinical outcomes for repeated rIPostC in ischemic stroke patients [24, 25].

We, therefore, hypothesized that rIPostC during the first few days following an ischemic stroke reduces infarct size. Since infarct size is strongly related to functional recovery [26], repeated rIPostC may be a simple and novel strategy to minimize the clinical impact of an ischemic stroke. Importantly, rIPostC is virtually cost-free, non-pharmacological, and non-invasive, and it can easily be added to the current treatment of stroke patients.

## Methods/design

### Aim

The aim of this trial is to examine the effect of repeated (twice daily) rIPostC during hospitalization on infarct size and clinical outcomes in ischemic stroke patients. In addition, we aim to explore the potential underlying (inflammatory) mechanisms for this effect of repeated rIPostC.

### Design

We will perform a randomized single-blind placebo-controlled clinical trial at the Radboud University Medical Centre (Radboudumc) in Nijmegen, the Netherlands. The study has been approved by the relevant ethical committee (CMO Arnhem-Nijmegen, registration number 2017–3711). This protocol has been registered with the Netherlands Trial Register (NTR6880).

### Patient population and randomization

Patients with an ischemic stroke who are being admitted to the emergency room of the Radboudumc are eligible for this study. Other inclusion criteria are: older than 18 years and a clinical diagnosis of an ischemic stroke (established by a neurologist, based on the World Health Organization criteria for stroke) [27]. Exclusion criteria include: unstable vital signs, admitted more than 12 hours after onset of symptoms, upper extremity injury, edema contra-indicating rIPostC, bilateral mastectomy, or axillary lymph node dissection. Patients with contra-indications for magnetic resonance imaging (MRI; e.g., those with a pacemaker, vascular clips, cochlear implants, or other implanted metal objects) will also be excluded because of the impossibility of assessing our primary outcome. All patients will provide written informed consent. For those patients who are not mentally capable of signing informed consent in the acute setting, oral assent will be obtained. This will allow the intervention to start while providing an opportunity for informed consent to be given when the patients or their caregivers are capable of making a well-considered decision. Patients who receive a change in diagnosis after inclusion will be excluded from the analysis of our primary outcome (infarct size).

After informed consent or oral assent has been given, randomization will be performed using a predefined table generated by the computer program SealedEnvelope. Patients will be randomized in a 1:1 ratio to rIPostC or sham conditioning by the coordinating investigator. Stratification will be performed for treatment received (thrombectomy, thrombolysis, or no revascularization treatment) to ensure equal allocation of these subgroups to rIPostC and sham conditioning.

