### Primary outcome measure

The primary outcome measure will be the infarct size on day 4 after admission (or at discharge if discharge is before day 4), which will be compared between the intervention and control groups. The infarct size will be evaluated by diffusion-weighted MRI brain imaging using a 1.5-tesla MRI scanner (Siemens® Avanto). The infarct size will be annotated manually and analyzed on a dedicated work station by a trained researcher under the supervision of a neuroradiologist.

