### Sample size calculation

The sample size was estimated based on two trials [34, 35], which had a similar stroke population. Based on our clinical experience, we expect that a difference of 15 cm^3^ in infarct size between the two randomized groups should be considered as a clinically important difference. From the two trials, we estimated a standard deviation of 36 cm^3^. Based on α = 0.05 and power β = 0.80, we calculated that we need *n* = 90 per study arm. To account for an expected drop-out rate of 10%, we will include 100 patients in each group. This group size is comparable with other trials [20, 36] with the same intervention (rIPostC) and primary outcome (infarct size).

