### Statistical analyses

Data will be analyzed according to an intention-to-treat analysis for all randomized patients. The primary outcome (infarct size) will be analyzed as a continuous variable using an independent *t*-test and presented with a 95% confidence interval for differences between both groups. Based on observations in previous research [2, 35, 37], we expect infarct size to be normally distributed. If the data are not normally distributed, a logarithmic transformation can be used. If this procedure fails, non-parametric alternatives will be used to analyze the data.

To analyze the mRS score, the odds ratio for a shift in the direction of a better outcome on the mRS will be assessed in both groups [38]. This ratio will be estimated with ordinal logistic regression and will be calculated for all possible cut-off values on the mRS.

For all continuous endpoints (e.g., quality of life, patient-reported outcomes, hospitalization, recurrent cerebrovascular accidents, and mortality, inflammatory, and vascular biomarkers), an independent *t*-test can be used to evaluate differences between usual care and rIPostC. We will consider the outcomes that are assessed at different time points (quality of life and patient-reported outcomes) as separate outcomes due to the possibility that there will be missing data after 12 months. If these continuous outcomes are, contrary to our expectations, not normally distributed, then a logarithmic transformation or non-parametric alternatives will be used.

Analyses will be done on the full data, and a sub-analysis will be performed excluding the patients who do not have a visible infarct on the MRI. Prior to analyses, the extent of missing data on all secondary outcomes will be evaluated and appropriate methods to handle missing data will be determined (e.g., multiple imputation). To ensure the analyses are blinded, all data will be blinded prior to analysis by an independent researcher. Full details of the analysis will be finalized in an analysis plan before the database is locked.

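### Excluding patients with a changed diagnosis from the primary analysis contradicts intention-to-treat for all randomised patients, and nothing shields that exclusion from allocation or the outcome MRI

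*Protocol article*

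**What the plan says.** Patients enter on "a clinical diagnosis of an ischemic stroke (established by a neurologist, based on the World Health Organization criteria for stroke"; the article does not require MRI confirmation at entry. The same section, Patient population and randomization, then states: "Patients who receive a change in diagnosis after inclusion will be excluded from the analysis of our primary outcome (infarct size". It does not say what counts as a change, who makes it, by when, on what evidence, or whether that person knows the allocation.

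The Statistical analyses section opens with: "Data will be analyzed according to an intention-to-treat analysis for all randomized patients". It does not refer back to the exclusion. It says the analyses use the full data, and that "a sub-analysis will be performed excluding the patients who do not have a visible infarct on the MRI". So a patient without a visible lesion is dropped only in that secondary analysis.

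On timing: "The primary outcome measure will be the infarct size on day 4 after admission (or at discharge if discharge is before day 4". This is the only MRI the article describes, and it comes after randomisation and treatment. On blinding, the Design section says: "We will perform a randomized single-blind placebo-controlled clinical trial". An independent researcher blinds the data before analysis.

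On numbers, the Sample size calculation uses a difference of 15 cm³ and an SD of 36 cm³ to reach 90 per arm, then adds: "To account for an expected drop-out rate of 10%, we will include 100 patients in each group".

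**The concern.** The two population rules apply to the same analysis and give different patient sets whenever a diagnosis changes after inclusion. A later analysis plan would have to break one of them, and the choice could then be made with the data in hand.

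The exclusion also takes place after randomisation and has no safeguards. Some diagnoses made on clinical grounds will be revised. The outcome scan is a plausible prompt for revision, because it is the only MRI described. Staff who deliver two different cuff pressures cannot be blind to allocation, and blinding the dataset before analysis comes too late to protect a diagnosis that has already been changed. If the decision depends on allocation or on the outcome scan, the groups compared are no longer the randomised groups. Patients with no lesion are the most exposed, and some of them may be treatment successes.

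**Working it through.** **The two rules side by side.** Take a randomised patient with a measured day-4 volume whose diagnosis is later revised to a non-stroke condition. The Statistical analyses section keeps this patient, as one of all those randomised. The Patient population and randomization section removes this patient. The article does not say which rule prevails. This conflict does not depend on any figure below.

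**The plan's own figure.** Inputs from the Sample size calculation: difference 15 cm³, SD 36 cm³, alpha 0.05 (two-sided assumed), power 0.80.

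- n per arm = 2 × (1.960 + 0.842)² × (36/15)² = 90.4; the t-based value is 91.4. The stated 90 reproduces within rounding.
- 90 / 0.90 = 100 per arm.
- Two-sample t-test power at 90 per arm is 79.4% (79.8% by the normal approximation).

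**What each rule does to power.** The rate m of changed diagnoses is not in the article, so 5, 10 and 15% are assumed. These patients are assumed to have zero infarct volume in both arms. The control mean μ among true strokes is also not given; 20 to 40 cm³ is assumed, with treated mean μ − 15.

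- *Exclusion on top of drop-out:* n = 90(1 − m).
- *Retention at 90 per arm:* difference = 15(1 − m). Variance in each arm = (1 − m) × 36² + m(1 − m) × (arm mean)². The two variances are averaged for the test.
- *Example, m = 10%, μ = 40:* control variance 1166.4 + 0.09 × 1600 = 1310.4; treated variance 1166.4 + 0.09 × 625 = 1222.7; average 1266.5, SD 35.6; difference 13.5; power 71.6%.

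| m | Excluded: n per arm | Excluded: power | Retained: difference (cm³) | Retained: power |
|---|---|---|---|---|
| 5% | 85.5 | 77.3% | 14.25 | 75.6–77.0% |
| 10% | 81 | 75.0% | 13.5 | 71.6–74.4% |
| 15% | 76.5 | 72.6% | 12.75 | 67.5–71.6% |

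With the control-arm variance in both arms and the normal approximation, the retained ranges at 5 and 10% are 75.3–77.1% and 70.6–74.3%. The conclusion does not change: retention costs at least as much power as exclusion.

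**What selective exclusion could do to the estimate.** Suppose a fraction x of the treated arm, all with zero volume, is removed and the control arm is untouched. The observed difference is μ − (μ − 15)/(1 − x).

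- μ = 20, x = 5%: 20 − 5/0.95 = 14.7 cm³.
- μ = 40, x = 10%: 40 − 25/0.90 = 12.2 cm³.

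Under these assumptions, a true 15 cm³ difference is attenuated to between 12.2 and 14.7 cm³. It does not change sign.

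**The case against.** The strongest reply is that no sentence makes the outcome MRI a ground for exclusion. The article speaks of a changed diagnosis, not of a negative scan, and it keeps patients without a visible infarct in the full-data analysis. That stands. A reader might infer that the outcome scan decides who is analysed; the article does not say so. What remains is that the retention of lesion-free patients does not protect one whose diagnosis is then revised, and nothing rules the scan out as the reason.

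A second reply is that removing non-stroke patients is sensible, and that adjudication details commonly belong in the analysis plan, which the article says will be finalised before database lock. This stands for the details. It does not cover two population statements that already conflict, and neither blinding to allocation nor blinding to the scan is stated for the diagnosis decision.

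A third reply is that exclusion preserves power better than retention. The table bears this out, so power is no argument against the exclusion. A reader might also infer that the stated 80% power is lost because of it. The article does not support that: the rate of changed diagnosis is not given, and the 10% drop-out allowance may already cover these patients.

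Finally, a reader might fear that dropping lesion-free patients could reverse the sign of the effect. That needs every zero volume removed from both arms, which describes the secondary visible-infarct analysis and not the primary rule. It is no measure of harm to the primary analysis.

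**Conclusion.** The contradiction is certain from the text: the article fixes two incompatible populations for the primary outcome and names no modified set. It is wrong as written and should be settled before the database is locked.

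The second part is a risk and not a demonstrated fault. With an open-ended exclusion after randomisation, clinical entry, a post-treatment scan as the only MRI described, and single blinding, allocation or the outcome scan may influence who is analysed. The illustrated attenuation, from 15 to between 12.2 and 14.7 cm³, rests on assumed control means of 20 to 40 cm³ and on 5 to 10% of the treated arm being selectively reclassified. None of these figures is in the article. The reason to act is the validity of the randomised comparison, not power.

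**What to change.** Replace the exclusion sentence in Patient population and randomization so that it agrees with Statistical analyses, in one of two ways.

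1. Preferred: all randomised patients with a measured infarct volume stay in the primary analysis, with 0 recorded if there is no lesion. Exclusion for a changed diagnosis becomes a sensitivity analysis.
2. If the exclusion stays primary: call the population modified intention-to-treat in both sections, and limit the exclusion to diagnosis changes judged blind to allocation and without the outcome MRI.

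Either way, restate the power for the chosen population, with an explicit assumed rate of changed diagnosis, and say whether the 10% drop-out allowance includes these patients.

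The cost is wording in the protocol and analysis plan, plus blinded adjudication under the second option. The first option dilutes the effect. At an assumed 5% of changed diagnoses, 15 becomes about 14.3 cm³ and power is about 75 to 77%, against 77% with exclusion. At 10% it is about 72 to 74%, against 75%.

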### Intervention: repeated remote ischemic postconditioning

A manual blood pressure cuff will be placed around the upper arm after the diagnosis of an ischemic stroke. All participants will receive four cycles of 5-min inflation of the blood pressure cuff, followed by 5 minutes of reperfusion. This procedure will be performed twice daily (morning and afternoon) during the hospitalization after the ischemic stroke for a maximum of 4 days. The level of cuff inflation differs between the groups. Cuff inflation in the rIPostC-group is >20 mmHg above systolic blood pressure, mediating full blockage of the arterial inflow. Subjects in the control group receive cuff inflation to 50 mmHg, which will not induce any ischemia. The intervention will be administered by a trained researcher. Blood pressure will be recorded before the intervention.

### Primary outcome measure

The primary outcome measure will be the infarct size on day 4 after admission (or at discharge if discharge is before day 4), which will be compared between the intervention and control groups. The infarct size will be evaluated by diffusion-weighted MRI brain imaging using a 1.5-tesla MRI scanner (Siemens® Avanto). The infarct size will be annotated manually and analyzed on a dedicated work station by a trained researcher under the supervision of a neuroradiologist.

### Secondary outcome measures

(1) The validated and frequently used Modified Rankin Scale (mRS) [2, 28, 29] will be used to assess clinical outcomes after 12 weeks. To assess clinical outcomes at the end of hospitalization, the validated National Institutes of Health Stroke Scale [30] will be used. Both scores are calculated as standard after a stroke and will be assessed by a clinical physician or nurse from the neurology department.

After 12 months, we will also examine hospitalization, recurrent (cerebro)vascular events, and mortality. These data will be extracted from patient files at the Radboudumc.

(2) To assess quality of life, participants will be asked to fill out two questionnaires after 12 weeks and 1 year. The first questionnaire is the Stroke-Specific Quality of Life Scale (SSQoL), which is reliable and reproducible for self-reported quality of life outcomes in stroke patients [31]. The second questionnaire is the TOPICS-SF (The Older Persons and Informal Caregivers Survey Short Form), which is used for assessing patient-reported outcome measures. The TOPICS-SF has been shown to be a valid and feasible questionnaire for older patients [32, 33].

(3) Venous blood will be sampled during the first presentation at the emergency department and at the end of hospitalization to explore the impact of daily rIPostC on vascular, immune, and anti-inflammatory pathways. Whole blood will be spun down and serum will be stored at −80 °C for future analysis. For further analysis of possible underlying mechanisms, urine will also be sampled and stored at −80 °C at the end of hospitalization.

An overview of all outcomes and corresponding measurements is presented in Fig. 1.

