Finally, we aim to include 200 patients. With approximately 250 stroke patients being admitted to the Radboudumc each year and with the eligibility criteria for this trial being very broad, we expect to recruit a sufficient number of patients during our recruitment period of ~2.5 years. We will include all stable adult stroke patients with a clinically diagnosed stroke who do not have contra-indications for an MRI or rIPostC and who are able to provide written informed consent. Based on this nonrestrictive participant selection, we expect no practical problems in recruiting a sufficient number of patients. An important advantage of our approach is that the results of our trial can be generalized to the larger population of stroke patients.

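### The stated analyses of NIHSS and mRS name no baseline value and no covariate, which costs precision on the secondary clinical outcomes but does not bias them

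*Protocol article*

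**What the plan says.** All references are to the protocol article.

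- **Timing (Secondary outcome measures).** The mRS "will be used to assess clinical outcomes after 12 weeks". For the other score: "To assess clinical outcomes at the end of hospitalization, the validated National Institutes of Health Stroke Scale [30] will be used". Both come from routine care: "Both scores are calculated as standard after a stroke and will be assessed by a clinical physician or nurse from the neurology department". No admission NIHSS and no pre-stroke mRS is mentioned. The same section does give the biomarkers a starting value: "Venous blood will be sampled during the first presentation at the emergency department and at the end of hospitalization".
- **Entry (Patient population and randomization; Discussion).** "Other inclusion criteria are: older than 18 years and a clinical diagnosis of an ischemic stroke". The exclusions set no NIHSS range and no limit on earlier disability. The Discussion describes the criteria as very broad: "We will include all stable adult stroke patients with a clinically diagnosed stroke who do not have contra-indications for an MRI or rIPostC". That sentence goes on to require the ability to give written consent, and unstable vital signs are an exclusion.
- **Stratification (Patient population and randomization).** By acute treatment only, in three levels: thrombectomy, thrombolysis or neither.
- **Analysis (Statistical analyses).** For the mRS, "the odds ratio for a shift in the direction of a better outcome on the mRS will be assessed in both groups", estimated by ordinal logistic regression; no covariate is named. For continuous endpoints an independent t-test is offered. NIHSS is not among the examples listed there. Full details are left to an analysis plan to be finalized before database lock.

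**The concern.** Admission severity and pre-stroke disability can be expected to predict the later NIHSS and mRS. With entry this broad, both will vary widely between patients. An analysis that uses neither leaves this spread in the error term, where it widens the confidence interval for the treatment effect. A t-test cannot take a covariate, and the ordinal model, which can, is given none.

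What is at stake is the precision of the clinical outcomes. The Discussion concedes that the trial is not powered for the mRS, so precision that costs almost nothing is worth having. It also says that the mRS scores will feed the power calculation of a later trial. Pre-stroke mRS raises a separate point of timing: an analysis plan written later can add a covariate, but it cannot recover a value that nobody recorded.

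**Working it through.** **The plan's own figure.** The sample size rests on infarct size: difference 15 cm³, SD 36 cm³, α = 0.05, power 0.80 (Sample size calculation).

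n per arm = 2 × [36 × (1.960 + 0.842) / 15]² = 90.4, so 91. The stated 90 gives 79.8% power, and 90 / 0.90 = 100 per arm after 10% drop-out. The figure reproduces with a two-sided test. The plan gives no SD, effect or power for NIHSS or mRS.

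**Inputs for the check.** From the plan: n = 90 per arm, two-sided α = 0.05. Assumed, because the plan gives nothing: a true effect of 0.35 SD, and a correlation r between baseline and later score of 0.3, 0.5 or 0.7. The score is treated as roughly continuous.

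**Precision.** Adjusting for a baseline with correlation r multiplies the residual variance by 1 − r². The effect in residual SD units becomes 0.35 / √(1 − r²). Two-sample t-test power at 90 per arm:

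| r | Residual variance | Effect in residual SD | Power |
|---|---|---|---|
| 0 (unadjusted) | 1.00 | 0.350 | 0.646 |
| 0.3 | 0.91 | 0.367 | 0.687 |
| 0.5 | 0.75 | 0.404 | 0.769 |
| 0.7 | 0.51 | 0.490 | 0.905 |

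**The same in detectable differences.** The smallest difference found with 80% power is (1.960 + 0.842) × √(1 − r²) × √(2/90). This is 0.418 SD unadjusted, and 0.398, 0.362 and 0.298 SD for r = 0.3, 0.5 and 0.7.

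**Sensitivity to the assumed effect.** For a true effect of 0.30 SD (normal approximation), power is 52% unadjusted and 56%, 64% and 81% for the same three correlations. The pattern does not depend on the choice of 0.35.

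**Chance imbalance.** The standardized baseline difference has standard error √(2/90) = 0.149, so its 95% range is ±1.96 × 0.149 = ±0.29 SD. The probability that it exceeds 0.2 SD in either direction is 18%. This ignores any balance gained from stratification. An imbalance at the edge of the range shifts the unadjusted outcome difference by r × 0.29: 0.15 SD for r = 0.5 and 0.20 SD for r = 0.7. Given such an imbalance, the unadjusted test's false-positive rate is about 13% and 21% respectively. Averaged over all randomizations it is 5%.

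**The case against.** The strongest case against has four parts.

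1. **The schedule is not available.** The text sends the reader to Fig. 1 for all measurements, and its caption lists both scores. A reader might infer from the text that no starting value exists. The documents do not support that: the figure is missing here, and the scores are described as routine, so an admission NIHSS may well be collected. This part stands, and the point is limited to what the text names and how it says the data will be analysed.
2. **Covariates can be set in the analysis plan.** This stands in part. Nothing in the article rules out adjustment, and the t-test wording is permissive. But the article does state methods, and they leave the prognostic information out. Nor can a later plan supply a pre-stroke mRS that was not recorded.
3. **There is no bias.** A reader might infer that imbalance could manufacture an effect. Randomization keeps the overall type I error at 5%. Only the result conditional on a particular imbalance is misleading, and stratification by acute treatment may balance severity to some degree. This stands in full.
4. **The size is assumed and the outcomes are secondary.** Both stand. The calculation is linear and carries over only roughly to a proportional-odds model, where adjustment changes the odds ratio being estimated. At r = 0.3 the gain is only four points of power.

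Two further inferences should also be avoided. A patient admitted with NIHSS 1 can still improve to 0 or worsen. A patient with pre-stroke mRS 3 to 5 still contributes to a shift analysis through the higher grades. Neither is lost to the comparison.

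**Conclusion.** The point holds as a matter of efficiency. The stated analyses name no baseline NIHSS, no pre-stroke mRS and no covariate, in a trial with very broad entry stratified only by revascularization treatment. The cost is precision on secondary outcomes: about 0.65 power unadjusted against 0.69 to 0.90 adjusted, for an assumed 0.35 SD effect, 90 per arm and assumed correlations of 0.3 to 0.7, on a linear approximation. The validity of the trial and its primary outcome are not affected. Whether the baseline values are collected cannot be settled without Fig. 1 and the full protocol.

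**What to change.** - **NIHSS at the end of hospitalization:** analyse with admission NIHSS and the stratification factor as covariates, by ANCOVA or, if the scores are skewed, an ordinal or rank-based equivalent.
- **mRS at 12 weeks:** include admission NIHSS, the stratification factor and, if recorded, pre-stroke mRS in the ordinal logistic model.
- **Data collection:** record pre-stroke mRS at admission if this is not already done, and state that the admission NIHSS is taken as the baseline value.
- **Reporting:** give the unadjusted results as supportive.

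The cost is analysis wording and one history item from patient or caregiver. A few patients will lack a value, so a rule for missing covariates is needed. The adjusted odds ratio is conditional on the covariates and should be labelled so, in particular if it informs the later trial. The Trial status section reports three patients recruited at first submission, when little would have been lost by adding the item. For patients already past admission, the pre-stroke grade would have to be reconstructed, which is weaker.
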